### Randomization and blinding

2.6

Participants will randomly be allocated to active-taVNS treatment or sham taVNS groups at a 1:1 ratio, based on a computer-generated random number sequence. The allocation process is strictly confidential and managed by administrative personnel uninvolved in study design and implementation. Each participant will be assigned a unique, de-identified alphanumeric code, encompassing the research center code, enrollment order, and randomization group identifier, ensuring data traceability. A designated research coordinator will maintain sealed, sequentially numbered opaque envelopes containing randomization assignments. Immediately before entering the operating room, a blinded circulating nurse will open the envelope to determine group assignment. Following verification of the group allocation details, the envelopes will be resealed, and this procedure will be conducted without disclosing the information to the patients. To ensure blinding, we will informed patients during preoperative consultation about potential sensory experiences during treatment, including sensations of pricking, needle-like stimulation, warmth, and vibration. We will explicitly emphasize that individual perception of stimuli varies significantly and that sensation intensity should not be used to assess treatment efficacy. Moreover, all stimulation devices will be designed with uniform appearance, with differences limited to electrical output parameters, thereby further preserving the integrity of the blinding procedure. The device will be preset to patient-specific maximum tolerable parameters by independent researchers not involved in the research, and will remain in a black screen state upon entering the operating room. All individuals involved in outcome assessment, data analysis, surgical procedures, and study participants remained blinded to group allocation. With regard to the initial administration of stimulation during hepatic portal occlusion, standard practice at this institution involves the surgeon informing the anesthesiologist and circulating nurse about surgical progress at this stage. However, these personnel were not provided with details regarding the specific stimulation protocol, thereby ensuring the maintenance of blinding within the surgical team throughout the procedure. Prior to study commencement, outcome assessors will accept rigorous blinding training, familiarizing themselves with assessment procedures and standards to minimize subjective influences on results.

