## Introduction

1

Liver cancer ranks as the sixth most prevalent malignant tumor worldwide globally and is the third leading cause of cancer-related mortality (1). Epidemiological projections anticipate a 55% global increase in incidence, with 81% of new cases and 80% of related deaths concentrated in Asia and Africa. China, which bears one of the highest liver cancer burdens worldwide, faces substantial challenges in the prevention and management of the disease (2). Among liver tumors, benign hepatic hemangiomas are typically asymptomatic; however, when these tumors reach a significant size, they may cause compressive symptoms and potentially lead to severe complications, such as tumor rupture and life-threatening hemorrhage (3). Clinical studies with long-term follow-up of 236 patients diagnosed with hepatic hemangiomas demonstrated that 61% exhibited tumor growth, indicating a statistically significant progression rate (4). Progressively enlargement of hepatic hemangiomas is now considered an indication for surgical intervention (3). In patients presenting with localized hepatocellular carcinoma or hepatic hemangioma, partial hepatectomy allows for complete tumor resection while preserving adequate liver volume, thereby contributing to improved patient prognosis (5–7). However, several perioperative factors—including manipulation of the liver parenchyma during surgery, intermittent occlusion of the portal vein leading to hepatic ischemia–reperfusion injury (HIRI), intraoperative massive blood loss and transfusion, and chronic perioperative stress—can trigger and aggravate hepatic dysfunction, potentially leading to postoperative liver failure and increased mortality (5, 8, 9). A meta-analysis of 32 studies involving 19,503 patients reported considerable variability in post-hepatectomy complication rates. Specifically, minor hepatectomies were associated with hepatic dysfunction and severe complication rates ranging from 7.2 to 21.6%, whereas major hepatectomy showed an overall severe complication rate of 38.8%. In-hospital mortality was reported at 5.9%, with 30-day and 90-day mortality rates of 4.6 and 6.1%, respectively. Patients with compromised residual liver function and insufficient liver volume exhibit significantly rates of higher morbidity and mortality (10). A subsequent meta-analysis of 37 studies encompassing a total of 14,096 patients confirmed a significant association between postoperative severe hepatic dysfunction, liver failure, and decreased overall survival as well as disease-free survival (11). Therefore, the implementation of effective perioperative hepatoprotective strategies is of critical importance. In contemporary clinical practice, anesthesia preconditioning (APC) and ischemic preconditioning (IPC) are recognized as potential hepatoprotective interventions (12, 13). However, due to ongoing controversies regarding the clinical efficacy of IPC, its routine use remains limited. Notably, dexmedetomidine-based APC has shown potential in preserving hepatic function following partial hepatectomy, however, further validation through large-scale, multicenter clinical trial is necessary to confirm its long-term efficacy (12, 14, 15).

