### Data collection and management

2.12

These data will be recorded in a case report form (CRF). Preoperative information includes comprehensive demographic data, medical history, current health status, surgical type, nutritional control status scoring (including preoperative hemoglobin levels and lymphocyte count), CAM, SAS, FRAIL and FSS scores. Additionally, preoperative liver and kidney function indicators, coagulation function parameters and inflammatory markers will be collected. Intraoperative data will encompass detailed metrics such as blood loss, urine output, ischemic occlusion frequency and duration, mean arterial pressure (MAP) and central venous pressure (CVP) during occlusion and reperfusion phases, extent of hepatectomy [Hepatectomy is classified as minor when involving up to four wedge resections or two segmental resections, and major when exceeding these criteria, such as left or right hemihepatectomy (43)], detailed medication records, and surgical and anesthesia duration. Postoperative data will include liver and kidney function, inflammatory markers, NRS for pain intensity, QoR-15 for overall recovery assessment, CAM and FSS scores for delirium and fatigue incidence, and gastrointestinal function recovery data.

After the trial, all participant data will be analyzed by an independent, professionally trained investigator who was not involved in any aspect of the experiment. Personnel responsible for perioperative follow-up and blood sample collection were blinded to group allocation and will not participate in interventions. Following sample collection, specimens will be centrifuged, classified, and recorded in an encrypted Excel spreadsheet stored on an iPad. Test results will be subsequently entered into the same Excel file. An independent investigator collected pre-, intra-, and post-operative questionnaire data, initially recording them on paper case report forms, then transcribing them into a Word document on the iPad. In accordance with national regulatory requirements, original samples will be stored in a dedicated anesthesia freezer pending authorized access. The iPad containing follow-up information, case report forms, and other sensitive data will be password-encrypted and secured in a locked cabinet, accessible only to authorized personnel for data entry, processing, and analysis.

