### Sample size

2.13

Sample size was calculated using PASS 15.0 software. The primary outcome measure was ALT level on postoperative day 2. Preliminary data showed a mean ALT level of 249.8 ± 147.9 U/L after partial hepatectomy. In a pre-experimental phase, taVNS interventions reduced ALT to 174.9 ± 103.5 U/L (approximately 30% reduction). With a significance level (*α*) of 0.05 and statistical power (1 − *β*) of 90%, a two-sided test determined a minimum sample size of 63 participants per group. Accounting for a 10% potential dropout rate, we plan to recruit 140 patients and randomly allocate them to active-taVNS and sham taVNS groups. Regarding the validation of the Minimal Clinically Important Difference (MCID), we estimated the MCID using a stepwise approach based on previous research methods (44). In this experiment, the sham taVNS group’s mean ALT ± standard deviation on postoperative day 2 was 249.8 ± 147.9 U/L, while the active-taVNS group was 174.9 ± 103.5 U/L, with a pooled standard deviation of 127.64. Conventionally, the MCID range is typically set between 0.2 and 0.5 times the pooled standard deviation, resulting in a reasonable MCID interval of 25.53 to 63.82. The mean difference between groups (*Δ*) was 74.9. When the intergroup difference exceeds the upper limit of the MCID, it indicates that the observed effect difference has clinical significance, thus supporting the reasonableness of the MCID determination.

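### The day-2 ALT comparison is planned without resection extent in either the allocation or the test, which costs precision but causes no bias; a pre-specified model with planned extent and baseline ALT would recover most of it

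*Protocol article*

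**What the plan says.** On allocation, section 2.6 of the protocol article says: "Participants will randomly be allocated to active-taVNS treatment or sham taVNS groups at a 1:1 ratio, based on a computer-generated random number sequence". It then describes custody, coding and the numbered opaque envelopes. It mentions no strata, blocks or minimisation factors, but it does not say in words that the sequence is unstratified.

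On analysis, section 2.14 names one two-group comparison for continuous data: a t-test if the data look normal, otherwise a Mann–Whitney U test, both without covariates. Multiple linear or logistic regression is mentioned in general, with no covariates and no link to the primary outcome.

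On resection extent:
- The Introduction cites a meta-analysis with rates of 7.2 to 21.6% for hepatic dysfunction and severe complications after minor resection, "whereas major hepatectomy showed an overall severe complication rate of 38.8" per cent.
- Section 2.12 supplies a definition, "Hepatectomy is classified as minor when involving up to four wedge resections or two segmental resections", and calls anything beyond that major. Extent is listed among the intraoperative data. The nearest preoperative item is surgical type.

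On size, section 2.13 gives the planning values: "Preliminary data showed a mean ALT level of 249.8 ± 147.9 U/L after partial hepatectomy" and "taVNS interventions reduced ALT to 174.9 ± 103.5 U/L (approximately 30% reduction". It concludes that "a two-sided test determined a minimum sample size of 63 participants per group", with 140 recruited to allow for 10% dropout.

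**The concern.** The protocol itself presents extent as prognostic for complications, and it classifies and collects it. As written, extent is then used nowhere in the primary comparison. If ALT also differs between minor and major resections, two things follow:
- Part of the between-patient spread in day-2 ALT is explainable but stays in the error term.
- In the one trial that is run, a chance surplus of major resections in one arm moves the observed ALT difference, and an unadjusted test cannot correct for it.

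A reader who sees uneven extent in the baseline table will ask for an adjusted result. An adjustment chosen after unblinding carries much less weight than one fixed beforehand.

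**Working it through.** **1. The plan's own sample size.** Inputs from section 2.13: means 249.8 and 174.9, SDs 147.9 and 103.5, two-sided alpha 0.05, power 90%.
- Difference = 249.8 − 174.9 = 74.9.
- Pooled SD = √[(147.9² + 103.5²)/2] = 127.65 (the article has 127.64).
- Normal approximation: n per arm = 2(1.960 + 1.282)² × 127.65²/74.9² = 61.0, so 62. With the noncentral t it is 63 (power 90.5%); the Welch version also gives 63 (90.4%).
- 2 × 63 = 126, and 126/0.90 = 140.

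The stated figures reproduce.

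**2. Assumptions.** The documents give neither the share of major resections (p) nor the ALT gap between major and minor resections (D). I take p = 0.2 to 0.5 and D = 50 to 150 U/L.

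**3. Chance imbalance with 63 per arm.** The SD of the difference in proportion major is √[2p(1 − p)/63]: 0.0713 at p = 0.2, 0.0816 at 0.3 and 0.0891 at 0.5. Exact binomial probabilities over p = 0.2 to 0.5:
- imbalance of 10 points or more: 15–25% of trials
- 15 points or more: 3–9%
- 20 points or more: 0.5–2.6%

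**4. Shift in the ALT contrast.** Shift at the 95% limit = 1.96 × SD of imbalance × D.
- Smallest: 1.96 × 0.0713 × 50 = 7.0 U/L, or 7.0/74.9 = 9% of the planned difference.
- Middle (p = 0.3, D = 100): 1.96 × 0.0816 × 100 = 16.0 U/L, or 21%.
- Largest: 1.96 × 0.0891 × 150 = 26.2 U/L, or 35%.

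For scale, the standard error of the unadjusted difference is 127.65 × √(2/63) = 22.7 U/L, so the middle shift is 16.0/22.7 = 0.7 standard errors.

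**5. Variance explained.** R² = p(1 − p)D²/127.65². At p = 0.3 and D = 100 this is 0.21 × 10,000/16,293 = 0.129. Adjustment is then worth a factor of 1/(1 − 0.129) = 1.15 in sample size.

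**6. Simulation.** 6,000 trials per scenario, 63 per arm, normal ALT, total SD held at 127.6, true difference 74.9, extent as the only covariate. Monte Carlo error on power near 90% is about 0.4 points. Power:

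| p, D | Simple, unadjusted | Simple, adjusted | Stratified, unadjusted | Stratified, adjusted |
|---|---|---|---|---|
| 0.3, 50 | 90.8% | 91.4% | 90.7% | 91.3% |
| 0.3, 100 | 90.5% | 93.8% | 91.7% | 93.7% |
| 0.4, 150 | 90.2% | 97.8% | 94.2% | 97.9% |

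Under no effect, with simple randomisation:
- The mean estimate was about 0, and the unadjusted test rejected in 4.6–5.3% of trials.
- The SD of the estimate fell with adjustment from 22.8 to 21.4 (p = 0.3, D = 100) and from 22.7 to 18.9 (p = 0.4, D = 150).

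Stratifying while keeping the unadjusted t-test was conservative, rejecting in 1.6–4.2%.

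**7. Scale.** The two planning coefficients of variation are nearly equal: 147.9/249.8 = 0.592 and 103.5/174.9 = 0.592. This fits a proportional effect with a common SD on the log scale, and so favours log ALT as the response.

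**The case against.** The case against has real force.

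- **Nothing is invalid.** Simple 1:1 allocation in a single-centre trial of 140 is an acceptable design. Chance imbalance is already covered by the standard error, and the planning SD presumably includes whatever mix of extents the preliminary patients had. This stands.
- **Stratification itself gains almost nothing.** Once extent is in the model, power is 93.7% with it and 93.8% without. This stands too, so changing the envelopes during recruitment is hard to justify on efficiency.
- **Covariates may be in an analysis plan not shown.** This stands in part. A missing covariate list would be no finding. The point is that the only two-group comparison the article names for a continuous outcome is unadjusted. If the analysis plan already has an adjusted primary model, citing it settles the matter.
- **The size is assumed.** No ALT figure by extent appears anywhere, and the Discussion lists a restricted variety of hepatectomy types as a limitation, so the share of major resections could be low. The gain would then be nearer the bottom of the range.

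A reader might also infer three stronger things that the text does not support. First, that allocation is known to be unstratified: this is inferred from silence in a condensed article. Second, that planned extent is known to be fixed before allocation: extent is listed as intraoperative. Elective scheduling and a preoperative surgical-type item make a prior plan likely, not certain. Third, that the protocol calls extent a main driver of liver injury: its figures concern complications, the minor and major rates are not for the same outcome, and extent is absent from the Introduction's list of causes of hepatic dysfunction.

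**Conclusion.** The point holds as one of efficiency and credibility, not validity. As described, the primary day-2 ALT comparison ignores a recorded factor that the protocol links to worse outcome. It would be wrong to conclude that the result will be biased, that the 5% error rate fails or that the trial misses its 90% power; the checks show none of these.

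The cost is lost precision, plus exposure of this one trial's ALT difference to a chance shift of about 7 to 26 U/L at the 95% limit, against 74.9 planned. Adjusting for extent lifts power from 90.5% to 93.8% in the middle scenario, by under one point if the ALT gap is 50 U/L, and to about 98% if 40% of resections are major and the gap is 150 U/L. All of these rest on the assumed share of major resections and ALT gap, and on normal data with extent as the only covariate. The further gain from baseline ALT has not been quantified.

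**What to change.** Before unblinding, and preferably before the interim look described in section 2.11, pre-specify the primary analysis as a linear regression of day-2 ALT, for example log ALT, on treatment, with planned minor/major extent (section 2.12 definition) as a factor and baseline ALT as a covariate, for all 140 patients. Take extent from the preoperative surgical plan, not from the resection achieved, so that it is fixed before allocation. State in section 2.6 whether allocation was stratified or blocked; if it was stratified, put that factor in the model as well. On the log scale the effect is reported as a ratio of geometric means.

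The cost is a short amendment and two model terms. Baseline ALT is already drawn at t0. The main burden is that planned extent must be written down before the envelope is opened, and retrieved from preoperative records for patients already randomised. A second envelope series for the remaining patients is optional: it guards against visible imbalance but adds little once the model term is in place. It should not be combined with an unadjusted test.

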### Study design

2.1

This is a single-center, prospective, double-blind, randomized controlled clinical trial that will be conducted at the Affiliated Hospital of Xuzhou Medical University. A total of 140 patients scheduled for elective partial hepatectomy will be enrolled. The study protocol has received ethical approval from the Ethics Committee of the Affiliated Hospital of Xuzhou Medical University (approval number: XYFY2024-KL521-01) and has been registered with the Chinese Clinical Trial Registry (http://www.chictr.org.cn, Registration number: ChiCTR2400092005). Recruitment of participants is currently in progress, following strict adherence to predefined inclusion and exclusion criteria. Written informed consent will be obtained from all participants prior to enrollment. The study follows the Standard Protocol Items: Recommendations for Interventional Trials (SPIRIT) guidelines (Supplementary material 1) (29). The flow of patient recruitment, intervention, and outcome measurement is summarized in Figure 1.

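### Section 2.6 calls the nurse who opens the allocation envelope blinded, and puts a randomisation group identifier in every participant code, which contradicts or endangers the blinding it claims

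*Protocol article*

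**What the plan says.** All references are to the protocol article.

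- Study design (2.1): "This is a single-center, prospective, double-blind, randomized controlled clinical trial".
- Randomization and blinding (2.6), on who is blinded: "All individuals involved in outcome assessment, data analysis, surgical procedures, and study participants remained blinded to group allocation".
- 2.6, on the envelope: "a blinded circulating nurse will open the envelope to determine group assignment". The allocation is then verified and the envelope resealed. The only non-disclosure stated for this step concerns patients: "this procedure will be conducted without disclosing the information to the patients".
- 2.6, on the start of the first stimulation at portal occlusion: standard practice is "the surgeon informing the anesthesiologist and circulating nurse about surgical progress at this stage". The section adds that "these personnel were not provided with details regarding the specific stimulation protocol", and concludes from this that the surgical team stays blinded.
- 2.6, on the participant code: it is de-identified and alphanumeric, "encompassing the research center code, enrollment order, and randomization group identifier, ensuring data traceability".
- Data collection and management (2.12): "Personnel responsible for perioperative follow-up and blood sample collection were blinded to group allocation".

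**The concern.** Two stated procedures sit badly with the stated blinding.

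First, the person who learns the allocation is labelled blinded and stays in theatre during the operation and the first stimulation session. The surgeon and anesthesiologist working there make discretionary decisions, for example on fluids and vasoactive agents (section 2.8). If the arm became known to them, care could differ between arms.

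Second, a code used to trace a participant's data should carry nothing about the arm. If it does, anyone who handles coded material is at risk of unblinding. What could then be affected is the assessor-dependent secondary outcomes, such as CAM and I-FEED, and decisions to discontinue a participant, which section 2.5 leaves partly to the researchers.

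**Working it through.** No figure in the plan depends on this point, so the check compares the statements.

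**Step 1. The nurse.** Three statements in 2.6 are set side by side.

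| Statement | What it implies for the circulating nurse |
|---|---|
| The nurse opens the envelope to determine the assignment, and the allocation is verified | Knows the arm |
| The nurse is described as blinded, and all surgical personnel are declared blinded | Does not know the arm |
| Theatre staff, the circulating nurse included, lack details of the stimulation protocol | Relied on to show that the surgical team is blinded |

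The first row cannot hold together with the second, and it undercuts the use made of the third. Resealing the envelope does not remove what was read. This step needs no assumption.

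**Step 2. The code.** The stated elements are centre, enrolment order and randomisation group identifier. Three cases follow.

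- *The code stays with the allocation administrator.* No blinded person sees it, and there is no leak.
- *Blinded staff see the code and the identifier is readable.* Each code shows its arm directly.
- *Blinded staff see the code and the identifier is a masked two-value label, such as A or B.* The arm is not named, but patients are sorted into two visible groups. If those staff learn the arm of one patient, they can infer the arm of every other patient whose code they see.

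The article does not say which case applies. The stated purpose, data traceability, suggests that the code travels with the data, but section 2.12 does not say that it appears on the CRF, the sample tubes or the Excel file.

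**Step 3. How likely is one unblinding?** Section 2.7 starts unblinding promptly for complications that include ear pain and ear dermatitis. Section 2.11 does so when an adverse reaction is suspected during the intervention, and it lists dizziness among the potential events. The Discussion cites a review with 16.7% local symptoms and 1.4% dizziness or syncope.

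As an illustration, assume that these rates apply per participant in the active arm (140/2 = 70), that participants are independent, and that every such event triggers unblinding.

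- Dizziness or syncope only: 1 − (1 − 0.014)^70 = 1 − 0.373 ≈ 63% chance of at least one unblinding.
- Local symptoms: 70 × 0.167 ≈ 12 expected events, so at least one unblinding is nearly certain.
- If staff in practice do not unblind for such minor events, the chance could be close to zero.

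The range is wide, but under the written rules a single unblinding is not a remote event. The article does not say who learns the result.

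**The case against.** The strongest reply concerns the code. The article calls it de-identified and the allocation process strictly confidential, run by uninvolved staff. It never places the code on a CRF or sample, and labelling details are commonly left to the full protocol. This stands, and it is why the code is a conditional risk and not a demonstrated breach. It does not remove the point, because the article chose to state that a group element is in the code.

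For the nurse, one could suppose that the envelope holds only a device number. The text does not support that: the envelopes contain the randomisation assignments and are opened to determine the group.

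A reader might infer more than the documents show:

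- *That the double-blind design fails altogether.* Patients are not told the allocation, nothing gives the circulating nurse an assessment role, and section 2.12 keeps follow-up and sampling staff out of the interventions. What is shown is one mislabelled role and one risky code.
- *That one emergency unblinding decodes the other 139 participants (140 − 1).* This needs a constant two-value label, codes visible to blinded staff, an unblinding result that reaches those staff, and full enrolment by then. None of the first three is stated.
- *That the self-reported scales (QoR-15, NRS, SAS, FSS) are compromised.* These rest largely on the patient's own report, and nothing says that patients see or can read the code.

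The intention-to-treat analysis with multiple imputation (section 2.14) also limits the harm from selective removals, without abolishing it.

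**Conclusion.** Section 2.6 contradicts itself on the circulating nurse. The nurse who opens the envelope is not blinded, and the statement that all surgical personnel are blinded is wrong as written. This rests on the text alone and applies to every participant randomised in this way.

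The group identifier in the code is a second, conditional weakness. It matters if the code is visible to sample handlers, assessors or the analyst. With a masked label, it also requires that those staff learn of at least one unblinding.

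The size of any bias cannot be computed from the documents. The exposure is mainly in perioperative care, discretionary discontinuation and assessor-dependent secondary outcomes. Postoperative day 2 ALT is a laboratory value and less exposed, although differences in care or in discontinuation could still reach it. Recruitment is already in progress (section 2.1), so each further enrolment under the present wording adds to the records concerned.

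**What to change.** 1. Use centre plus enrolment number only as the participant code. The uninvolved administrator holds the code-to-arm key. Re-label existing records.
2. Have the independent researcher who presets the device open the envelope, and describe that person as unblinded. Because the sham group receives no current (section 2.9), whoever sets the output needs the allocation in any case. This person must have no role in surgery, care, assessment or analysis.
3. If the nurse keeps the task, call the nurse unblinded and correct the statement that all surgical personnel are blinded.

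The cost is a change of wording in section 2.6 and the re-labelling of records already made. No new staff are needed, and sample size and outcomes are untouched. Re-labelling cannot undo what staff may already have seen, so it is better done soon.
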